**3) How long will the subject identifiers be maintained in association with the research data?**

Until the infant is discharged from the hospital and the outpatient DEXA scan has been completed.

**C. Will research data that contains subject identifiers be disclosed to anyone at UNMC, TNMC, UNO or CHMC who is not listed in Section I of this application?**

☒ No

☐ Yes. Identify by name. [See Educational Guide – Biomedical Research \(PedsIRB\)](#)

**D. Will research data that contains subject identifiers be disclosed to any investigators outside of UNMC, TNMC, UNO or CHMC?**

☒ No

☐ Yes. Respond to the following:

1) Identify the investigator by name and affiliation.

2) Specify the subject identifiers which will be associated with the data.

3) Explain the necessity for this disclosure. [See Educational Guide – Biomedical Research \(PedsIRB\)](#)

**E. Will research data that contains subject identifiers be disclosed to any commercial sponsor, contract research organization (CRO) or Data and Safety Monitoring Board (DSMB)?**

☒ No

☐ Yes. Respond to the following:

1) Identify by name and affiliation.

2) Specify the subject identifiers which will be associated with the data.

3) Explain the necessity for this disclosure. [See Educational Guide – Biomedical Research \(PedsIRB\)](#)

**F. Will research data that contains subject identifiers be disclosed to any other external organization or entity (e.g., NCI cooperative groups)?**

☒ No

☐ Yes. Identify by name.

**G. Will research data be shared with third party payers?**

☒

**No**

☐

**Yes.** [See Educational Guide – Biomedical Research \(PedsIRB\)](#)

**H. For what duration of time will research data be subject to disclosure to the persons or groups identified above?** [See Educational Guide – Biomedical Research \(PedsIRB\)](#)

**I. What provisions will be in place to protect the subject's privacy?** [See Educational Guide – Biomedical Research \(PedsIRB\)](#)

Consent will be obtained in the patient's individual private room. Unauthorized personnel will not be involved in consenting patients and will not have access to patient identifiers for the purposes of the study. Specific subject identifiers will not be directly associated with the research data. The patients will be referred to as de-identified numerical subjects

**J. Does this research involve data banking at UNMC, TNMC, UNO or CHMC for future use or for purposes that are not integral to the current research?**

☒ No

☐ Yes. Complete and attach *Addendum I*.

**RISK/BENEFIT ASSESSMENT (16-22)**

**16. POTENTIAL RISKS**

**What are the potential risks associated with each research intervention? If data are available, estimate the probability that a given harm may occur. See Educational Guide – Biomedical Research (PedsIRB)**

This study will be presented as a greater than minimal risk for physical and psychological harm.

Supplemental vitamin D3 400 IU or 800 IU will be given to the respective groups. Hypercalcemia has been associated with supplementation resulting in serum levels of above 150 ng/mL. Based on preliminary data, we do not expect our supplementation protocol to achieve 25(OH)D levels of >30 ng/mL. We would not expect this dose of vitamin D to carry any potential risk to the subject, in fact this dosing is consistent with an American Academy of Pediatrics guideline that recommends all term, healthy infants consuming less than 1000 mL of formula a day receive 400 IU vitamin D3 supplementation, and the European Society for Gastroenterology, Hepatology, and Nutrition recommendation that premature infants receive 1000 IU/day of vitamin D3 (18).

Hypersensitivity to vitamin D resulting in hypercalcemia can occur in individuals with primary hyperparathyroidism. Infants with this condition would be excluded from the study.

Study subjects would also have increased blood draws for study purposes compared to infants not enrolled in the study. Each subject would have approximately 4 mL of blood drawn over the course of 8 weeks (2 mL per 4 weeks) that a non-study infant would not be exposed to. Increased phlebotomy can result in anemia and risk of infection. Many blood draws are for routine care in the Intensive Care Nursery, so blood for study purposes would be drawn at the same time as patient care labs whenever possible to avoid a painful procedure for the infant. Collection of a urine sample represents minimal risk to an infant, there is a small risk of skin breakdown which is minimized by changing the collection bag every 24 hours.

DEXA systems assess body composition by measuring the differential absorption of x-rays at two frequencies and can separate tissue into fat, lean, and bone mineral. DEXA is relatively easy to administer and uses a very low level of radiation, approximately 1/6 to 1/2 the exposure from a standard chest x-ray. At doses much higher than these infants will receive, radiation is known to increase the risk of developing cancer after many years. At the doses these infants will receive, it is very likely that we will see no effects at all.

All of the proposed risks and benefits will be presented to the mother of the infant using oral and printed information prior to a request for an informed consent to participate in the study.

**17. RISK CLASSIFICATION**

**What is the overall risk classification of the research?**

- ☐ Minimal risk  
☒ Greater than minimal risk  
☐ Significant risk

*See Educational Guide – Biomedical Research (PedsIRB)*

## 18. MINIMIZATION OF RISK

- A. Will the research utilize procedures in order to obtain data which will be performed on the subjects in the course of their normal clinical care (i.e. for diagnostic or treatment purposes)?

☐ No

☐ Yes. Describe the procedures. *See Educational Guide – Biomedical Research (PedsIRB)*

The blood obtained at birth will be from the cord blood that is routinely drawn by the labor and delivery units at TNMC and stored at the patient's bedside in the NICU.

- B. Describe how potential risks will be minimized and how the subjects of the research will be monitored by the investigators and other research personnel to ensure their safety. *See Educational Guide – Biomedical Research (PedsIRB)*

Blood is drawn at regular and frequent intervals for patient management during an infant's intensive care nursery stay. Blood for study purposes is drawn at the same time as routine patient care labs whenever possible. Developmentally appropriate nursing interventions such as swaddling, pacifier use, or Sweet-Ease are used at the discretion of the nurse during lab draws to minimize the infant's discomfort.

Urine collection bags will be changed with every diaper change.

- C. Is there is a DSMB for this study?

☒ No. Complete question 18d below.

☐ Yes. Submit the DSMB charter or respond to the following information:

1) Membership composition

2) The authority of the DSM.

3) The timing of the DSMB meeting

4) The frequency of DSMB reports. *See Educational Guide – Biomedical Research (PedsIRB)*

- D. If there is no DSMB assigned to this study, describe the data monitoring plan. Specifically:

- 1) Who will perform the ongoing data and safety analysis?

The PIs will monitor the data on an ongoing basis for any instances of hypercalcemia or hypervitaminosis D. Subjects will be withdrawn from the study should any abnormalities in calcium or vitamin D metabolism occur.

Hypercalcemia (as defined by a serum calcium as  $\geq 12.5$  mg/dL or an ionized calcium of 1.35) will be used as the main measure of toxicity, as hypercalcemia is the primary adverse event associated with vitamin D toxicity. These values occur in real time.

25(OH)D levels will also be monitored for 25(OH)D levels above 150 ng/mL. Blood for 25(OH)D levels will be transported to the Creighton Osteoporosis Research Center (CUORC) for analysis. This blood is analyzed when the CUORC has enough samples to fill out a run of 40 samples, including any other samples they may be analyzing. Therefore, in our previous experience, blood samples for 25(OH)D levels occurred more than once a month.

**2) What is the frequency of data analysis?**

*See Educational Guide – Biomedical Research (PedsIRB).*

**E. Describe the specific subject withdrawal criteria. If *none*, provide an explanation. *See Educational Guide – Biomedical Research (PedsIRB)***

A subject will be withdrawn from the study at the request of the parent or attending neonatologist. A subject would be withdrawn from the study with the diagnosis of GI, liver, or kidney disease, inborn errors of metabolism, parathyroid disease, disorders of calcium metabolism, and any condition requiring treatment with seizure medication or steroids. A subject could also be withdrawn at the request of the parent or guardian. Ongoing monitoring of the data will allow for any subject with lab abnormalities related to vitamin D or calcium to be withdrawn from the study. A subject would be withdrawn with a serum calcium above 12.5 mg/dl after initiation of the vitamin D, or a 25(OH)D level above 150 ng/mL.

**F. Describe the specific stopping rules for the research. If *none*, provide an explanation. *See Educational Guide – Biomedical Research (PedsIRB).***

The study would be stopped in the event that even a small amount of the infants enrolled in the study (>5 infants) developed hypercalcemia (serum calcium above 12.5, ionized calcium about 1.35) or hypervitaminosis D (25(OH)D levels above 150 ng/mL).

**G. Describe the auditing plan for the research (i.e., who will conduct the audit and how often). If *none*, provide an explanation. *See Educational Guide – Biomedical Research (PedsIRB)***

None

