### CHARACTERISTICS OF THE SUBJECT POPULATION (3-10)

#### 3. ACCRUAL

- A. What is the number of subjects that must complete the study and be evaluable in order to achieve the scientific objectives of the research?** [See Educational Guide – Biomedical Research \(PedsIRB\)](#)

40 NICU infants who are between 23 and 32 weeks gestational age must complete the study.

- B. What is the statistical or other justification for the number of subjects needed to complete the study?** [See Educational Guide – Biomedical Research \(PedsIRB\)](#)

Based on our previous study, NICU infants who received 400 IU/day of Vitamin D are expected to have a mean discharge serum 25(OH)D of 23.1 ng/ml (standard deviation=7.0). Conservatively, the 800 IU dose group is expected to have a mean discharge serum 25(OH)D of 30 ng/ml (SD=7.0) (SD estimated from our previous study data). Assuming a 0.05 level of significance, and a total drop-out rate of 10 percent; 40 NICU infants randomized to the two dose groups will provide 81 percent power to detect a difference between doses.

- C. What is the maximum number of subjects that will be consented at all sites under the oversight of the PedsIRB and what is the justification for this number?** [See Educational Guide – Biomedical Research \(PedsIRB\)](#)

A maximum of 40 infants who are between 23 and 32 weeks gestational age will be consented for the study.

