## METHODS AND PROCEDURES (11-15)

### 11. METHODS AND PROCEDURES APPLIED TO HUMAN SUBJECTS

- A. Does this protocol require tests to be performed for the purpose of determining subject eligibility which would not be *routinely* conducted as part of standard clinical care of the prospective subject?

☒ No

☐ Yes. Describe the tests to determine subject eligibility. [See Educational Guide – Biomedical Research \(PedsIRB\)](#)

- B. Indicate the study design by checking the appropriate boxes.

[See Educational Guide – Biomedical Research \(PedsIRB\)](#)

☐ Phase I

☐ Phase I/II

☐ Phase II

☐ Phase II/III

☐ Phase III

☐ Phase IV

☐ Other:

☐ Case-Control

☐ Cohort

☐ Cross-sectional

☐ Randomized, parallel group

☐ Randomized, cross-over

☐ Placebo-Controlled

☐ Single Blind

☒ Double Blind

☐ Triple Blind

- C. Describe sequentially all procedures, interventions and evaluations to be applied to subjects, including follow-up. [See Educational Guide – Biomedical Research \(PedsIRB\)](#)

Step 1: Recruitment and Informed Consent

Parents of infants admitted to the NICU who meet eligibility criteria will be approached by study personnel, information about the study will be given, and informed consent will be obtained.

Step 2: Collection of Baseline Data

A sample of cord blood drawn that is drawn at birth for other routine clinical use will be frozen and stored at -70 degrees for study analysis of 25(OH)D levels. Demographic information will be obtained, including gestational age, birth weight, length, circumference, race, ethnicity, and season of birth. This is routine NICU admission information that is not performed exclusively for research purposes.

Step 3: Randomization

Study pharmacist will be notified and eligible infants will be randomized to the 400 IU/day of 800 IU/day supplementation group. Vitamin D supplementation will begin when the infant reaches full enteral feedings. Both the investigators and the subjects will be blinded as to the treatment group.

Step 4: NICU Data Collection

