The primary endpoint for statistical analysis is serum 25(OH)D level at discharge. Analysis will be done using intent-to-treat strategy, where infants will be included in the group to which they were assigned regardless of compliance. The statistical analyses will be done with SAS software. P-values less than 0.05 will be considered statistically significant. Baseline characteristics (e.g. gender, season of birth) will be compared between the dose groups, stratified by race and gestational age, to ensure comparability of the groups using Mann-Whitney tests for continuous variables and Fisher's exact tests for categorical variables. Analysis of covariance (ANCOVA) will be conducted to test for differences in discharge serum 25(OH)D level between the dose groups while adjusting for known confounders (race, gestational age, gender and season of birth). If the overall F-tests are significant then pairwise comparisons will be made and p-values for these comparisons will be adjusted for multiple comparisons using Tukey's method. Correlation methods will be used to look at associations between 25(OH)D levels and iPTH levels at discharge. Descriptive plots will be used to evaluate changes in serum 25(OH)D levels. DEXA scan results evaluating total body minus head bone mineral density (BMD) will be compared between the two groups. Descriptive plots will be used to evaluate changes in serum 25(OH)D levels. All tests will be 2-sided and p-values <0.05 will be considered statistically significant.

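### Withdrawing randomised infants from the study, not just from the supplement, undermines the planned intent-to-treat analysis and can use up the 10 percent loss allowance

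*Protocol*

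**What the plan says.** Section 11.E commits to intent-to-treat: "infants will be included in the group to which they were assigned regardless of compliance". The endpoint is serum 25(OH)D at discharge; section 11.C Step 4 puts the last scheduled draw at 36 weeks corrected age.

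Section 18.E then lists grounds for leaving the study after enrolment:

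- Diagnoses: "A subject would be withdrawn from the study with the diagnosis of GI, liver, or kidney disease", followed by metabolic, parathyroid and calcium disorders.
- Any condition treated with anticonvulsants or steroids.
- Serum calcium above 12.5 mg/dL once vitamin D has started, or 25(OH)D above 150 ng/mL.
- Laboratory abnormalities related to vitamin D or calcium, with no limits given.
- A request from the parent or the attending neonatologist.

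Section 18.D has a similar open-ended rule: "Subjects will be withdrawn from the study should any abnormalities in calcium or vitamin D metabolism occur".

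On numbers, section 3.B reads "Assuming a 0.05 level of significance, and a total drop-out rate of 10 percent; 40 NICU infants randomized to the two dose groups" and claims 81 percent power. Section 3.A requires 40 completers, section 3.C caps consent at 40, and section 26.D expects no withdrawals.

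**The concern.** Most of these grounds repeat the exclusion criteria of section 9, applied after randomisation. An intent-to-treat analysis needs an endpoint value from each randomised infant as far as possible, including those who stop the supplement. The protocol knows only one kind of exit, from the study, and makes no provision for sampling afterwards. Followed as written, it leaves withdrawn infants without a final 25(OH)D value.

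Two things are at stake. The first is precision, because the sample has almost no slack and lost infants cannot be replaced under the consent cap. The second is comparability. Loss would follow illness, treatment or a judgement about vitamin D values, so the infants left at 36 weeks need not be comparable between arms. A statistical analysis plan can say how to handle missing values, but it cannot recover a sample that was never drawn.

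**Working it through.** **Inputs.** Means 23.1 and 30 ng/mL, SD 7.0 in both arms, 10% drop-out, 40 randomised (section 3.B); two-sided 0.05 (section 11.E: "All tests will be 2-sided and p-values <0.05 will be considered statistically significant"). The allocation ratio is not stated; 1:1 is assumed.

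**Stated power.** Evaluable: 40 × (1 − 0.10) = 36, or 18 per arm. Difference 30 − 23.1 = 6.9, which is 6.9/7.0 = 0.986 SD. Two-sample t-test: noncentrality 6.9 / (7.0 × √(2/18)) = 2.96 on 34 degrees of freedom, power 81.9%. The stated 81 percent reproduces.

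**Greater loss.** Same formula with the infants remaining. Rates above 10% are assumptions.

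| Loss | Evaluable (per arm) | Noncentrality | Power | Randomised N for 36 evaluable |
|---|---|---|---|---|
| 10% | 36 (18) | 2.96 | 81.9% | 40 |
| 20% | 32 (16) | 2.79 | 77.0% | 36/0.8 = 45 |
| 30% | 28 (14) | 2.61 | 70.9% | 36/0.7 → 52 |
| 40% | 24 (12) | 2.41 | 63.6% | 36/0.6 = 60 |

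**Slack.** The plan absorbs 40 − 36 = 4 losses. The binomial probability of 5 or more among 40 is 37% at a true rate of 10%, 74% at 15% and 92% at 20%.

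**Fixed 25(OH)D limit.** (150 − 30)/7.0 = 17.1 SD above the planned 800 IU mean. On the protocol's own figures this removes essentially nobody. The exposure lies in the diagnosis and treatment criteria and the undefined abnormality wording.

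**Bias, illustration only.** Simulated trials of 20 per arm, completers only, with an assumed correlation of 0.5 between 25(OH)D and a health score whose lowest values are withdrawn:

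- 20% loss in both arms: mean difference 6.92 against a true 6.9, so almost no bias.
- 10% loss at 400 IU and 30% at 800 IU: 7.98.
- 30% at 400 IU and 10% at 800 IU: 5.82.
- No true effect, with either unequal pattern: type I error about 7% instead of 5%.

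Unequal loss of that size shifts the estimate by about 1.1 ng/mL, in either direction.

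**Sections side by side.**

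- Forty completers (3.A), at most 40 consented (3.C) and 10% loss (3.B) cannot all hold: 40/0.9 requires 45. Section 26.D expects no withdrawals at all.
- Section 18.D counts calcium of 12.5 mg/dL or more as hypercalcemia; 18.E withdraws only above 12.5.
- The open-ended wording in 18.D and 18.E sits beside numeric limits without saying which governs.

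**The case against.** The protocol nowhere says that data collection stops at withdrawal or that collected data are discarded. Draws every 4 weeks may leave earlier values, and the analysis plan may deal with missing endpoints. A reader might infer that intent-to-treat is impossible; the text does not support that. It is undermined unless endpoint sampling continues, which can be arranged.

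Other stronger readings also fail:

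- **The diagnoses are common.** No incidence is given, so the 20% to 40% losses are a range, not a forecast.
- **High 800 IU values are removed, pulling that mean down.** The only numeric 25(OH)D limit is about 17 SD away, and section 16 does not expect levels above 30 ng/mL.
- **Deficiency itself triggers withdrawal.** Read literally, the abnormality wording could cover it. But the preceding sentence in 18.D points to high values ("The PIs will monitor the data on an ongoing basis for any instances of hypercalcemia or hypervitaminosis D"), and the study population was chosen for its high prevalence of deficiency. What remains is that the wording is undefined.
- **25(OH)D results unblind the investigators, who then withdraw selectively.** Section 11.C says "Both the investigators and the subjects will be blinded as to the treatment group", and the monitoring in 18.D sits awkwardly with that. However, the protocol does not say that the investigators read every numeric result. The planned separation is at discharge, too late to drive withdrawals, and no earlier separation is given.
- **Pre-dose loss biases the comparison.** Section 11.C lists randomisation before dosing ("Vitamin D supplementation will begin when the infant reaches full enteral feedings"), and the diagnosis criteria are not limited to dosed infants. Under blinding, though, loss before any dose cannot be caused by treatment; it costs power.

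Also fair: equal loss mainly costs power, and 20% loss costs about 5 points. What stands is that the protocol requires exit from the study and provides for no endpoint sample afterwards.

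**Conclusion.** The withdrawal rules in 18.D and 18.E conflict with the intent-to-treat commitment in 11.E. Endpoint values would be missing for reasons linked to illness and possibly to outcome; if loss differs by arm, the comparison is biased in a direction that cannot be known in advance. The 81% power holds only up to 4 losses in 40, a number exceeded with probability 37% even if the true rate is the planned 10%. At 20% to 40% loss, power is 77.0% to 63.6%.

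These figures rest on the protocol's means and SD, 1:1 allocation, and assumed loss rates. The bias figures rest further on an assumed correlation and show scale only. The conflict itself rests on the text alone. It should be settled before infants are enrolled, because uncollected samples cannot be recovered.

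**What to change.** 1. In 18.D and 18.E, define two events. Supplement stopped: the present clinical criteria and the neonatologist's authority unchanged. Withdrawn from study: parental permission withdrawn, or the neonatologist asks that study procedures end.
2. For every other randomised infant, keep the scheduled samples, including the 36-week draw, within the blood-volume limits of 11.C and 11.D. In 11.E, state that these infants are analysed in their assigned arm.
3. Reconcile the open-ended abnormality wording in 18.D and 18.E with the numeric limits there, and the two calcium statements with each other. No clinical limit is proposed here.
4. Reconcile sections 3.A, 3.B, 3.C and 26.D on expected losses and the number to be consented.

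Optional: randomise when full feeds are reached, which reduces pre-dose loss, and have the laboratory return only an alert flag for 25(OH)D to the investigators.

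Cost: protocol wording and draws already in the schedule. If withdrawn infants would now have no further sampling, the change means some continued research draws in infants who are off supplement and may be ill. Their values slightly dilute the contrast, as intent-to-treat accepts.

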**19. POTENTIAL BENEFITS TO THE SUBJECT**

**What are the anticipated benefits (if any) to the subjects that may reasonably be expected from participation in the research?** *See Educational Guide – Biomedical Research (PedsIRB).*

We anticipate subjects participating in the research will have increased 25(OH)D levels over non-participants. This may be associated with improved bone mineralization and an improved resistance to infection.

**20. POTENTIAL BENEFITS TO SOCIETY**

**What are the anticipated benefits (i.e., value) to society that may reasonably be expected to result from this research?** *See Educational Guide – Biomedical Research (PedsIRB)*

Suboptimal vitamin D levels are associated with poor bone health and increased incidence of respiratory tract infections, both of which are areas of high concern in a population of infants born prematurely or hospitalized. The results of this project will be of great interest to health care practitioners caring for infants, especially preterm infants, and could affect routine vitamin D supplementation practices. This research will add to the body of knowledge available regarding optimal 25(OH)D levels in this population. This research is novel because it investigates the relationship of VDBP in a population where very little is known.

